# Tacrolimus versus mycophenolate for AutoImmune hepatitis patients with incompLete response On first-line therapy (TAILOR study): a study protocol for a phase III, open-label, multicentre, randomised controlled trial

**DOI:** 10.1186/s13063-023-07832-w

**Published:** 2024-01-17

**Keywords:** AIH, Autoimmune hepatitis, Autoimmune liver disease, Tacrolimus, Mycophenolate mofetil, Randomised controlled trials, Second-line treatment, Complete biochemical response

## Abstract

**Background:**

Autoimmune hepatitis (AIH) is a rare, chronic inflammatory disease of the liver. The treatment goal is reaching complete biochemical response (CR), defined as the normalisation of aspartate and alanine aminotransferases and immunoglobulin gamma. Ongoing AIH activity can lead to fibrosis and (decompensated) cirrhosis. Incomplete biochemical response is the most important risk factor for liver transplantation or liver-related mortality. First-line treatment consists of a combination of azathioprine and prednisolone. If CR is not reached, tacrolimus (TAC) or mycophenolate mofetil (MMF) can be used as second-line therapy. Both products are registered for the prevention of graft rejection in solid organ transplant recipients. The aim of this study is to compare the effectiveness and safety of TAC and MMF as second-line treatment for AIH.

**Methods:**

The TAILOR study is a phase IIIB, multicentre, open-label, parallel-group, randomised (1:1) controlled trial performed in large teaching and university hospitals in the Netherlands. We will enrol 86 patients with AIH who have not reached CR after at least 6 months of treatment with first-line therapy. Patients are randomised to TAC (0.07 mg/kg/day initially and adjusted by trough levels) or MMF (max 2000 mg/day), stratified by the presence of cirrhosis at inclusion. The primary endpoint is the difference in the proportion of patients reaching CR after 12 months. Secondary endpoints include the difference in the proportion of patients reaching CR after 6 months, adverse effects, difference in fibrogenesis, quality of life and cost-effectiveness.

**Discussion:**

This is the first randomised controlled trial comparing two second-line therapies for AIH. Currently, second-line treatment is based on retrospective cohort studies. The rarity of AIH is the main issue in clinical research for alternative treatment options. The results of this trial can be implemented in existing international clinical guidelines.

**Trial registration:**

ClinicalTrials.gov NCT05221411. Retrospectively registered on 3 February 2022; EudraCT number 2021–003420-33. Prospectively registered on 16 June 2021.

## Administrative information

Note: the numbers in curly brackets in this protocol refer to SPIRIT checklist item numbers. The order of the items has been modified to group similar items (see http://www.equator-network.org/reporting-guidelines/spirit-2013-statement-defining-standard-protocol-items-for-clinical-trials/).

**Table Taba:** 

Title {1}	Tacrolimus versus mycophenolate for AutoImmune hepatitis patients with incompLete response On first line therapy: a Randomised trial (TAILOR study)
Trial registration {2a and 2b}.	EudraCT 2021–003420-33 ClinicalTrials.gov Identifier: NCT05221411 EU-CT number: 2023-509491-42-00
Protocol version {3}	Version 2.9, 28-09-2021.
Funding {4}	Grant from ZonMw, number: 10140022010001 And funding from Chiesi Pharmaceuticals b.v. (project number: PA 2019–71111/[name])

Role of sponsor {5c}	The funders have no role in the study design, collection, or management of data. Neither ZonMw nor Chiesi Pharmaceuticals b.v. have access to coded of decoded data. The funders do not play a role in the analysis or publication process of this study.

## Introduction

### Background and rationale {6a}

Autoimmune hepatitis (AIH) is a rare, chronic inflammatory disease of the liver. It is characterised by the presence of circulating autoantibodies, elevated immunoglobulin gamma (IgG), elevated aspartate and alanine aminotransferases (AST and ALT respectively) and interface hepatitis in histology. The simplified or original diagnostic criteria for AIH are used for the diagnosis [1, 2]. Clinical manifestation is very heterogeneous, differing from asymptomatic raised liver enzymes and nonspecific symptoms as fatigue and arthralgia to acute (on chronic) liver failure [3].

The goal of treatment is achieving and maintaining clinical remission. Remission of disease is important to prevent further progression of disease to fibrosis and eventually cirrhosis, decompensated cirrhosis, liver transplantation or liver-related mortality [4–10]. Complete biochemical response (CR) is defined as serum ALT, AST and IgG below the upper limit of normal (ULN) [11, 12].

Standard treatment consists of prednisolone (0.5–1 mg/kg/day) and azathioprine (1–2 mg/kg/day) according to the European guidelines [11]. In case of an adequate response to therapy, steroids can be tapered gradually. In 80–90% of the patients on first-line treatment, adequate biochemical response is seen with a prompt decrease of aminotransferases [11], although around 50% have not achieved CR after a year.

Treatment of patients with an incomplete response or intolerance to prednisone (or budesonide) and azathioprine (or 6-mercaptopurin or 6-thioguanine) remains a clinical challenge. As incomplete response occurs in 20–50% of the patients (50% 1 year after treatment, 20% at 3 years) [13, 14], second-line treatment options are needed. The scientific evidence for second-line therapy currently consists of expert opinions, case series and retrospective studies. In this study, we aim to prospectively compare the biochemical response rate of tacrolimus (TAC) versus mycophenolate mofetil (MMF), both combined with glucocorticoids, as second-line therapy in AIH without CR on first-line therapy.

## Objectives {7}

The primary objective of this study is to investigate the difference in the proportion of patients in complete biochemical response (CR) after 12 months of treatment with TAC compared to MMF, both with glucocorticoids, in patients with AIH and an incomplete response to at least 6 months of first-line treatment.

CR is defined as serum ALT, AST and IgG below the upper limit of normal, conforming to European Association of the Study of the Liver (EASL) guidelines [11].

## Trial design {8}

This is a study protocol for a phase III, multicentre, open-label (i.e. non-blinded) randomised, controlled superiority trial, with parallel group assignment and 1:1 allocation. The protocol is written in accordance with the Standard Protocol Items: Recommendation for Interventional Trials (SPIRIT) guidelines [15]. Figure 1 shows a schematic diagram of the trial as the SPIRIT figure.

**Fig. 1 Fig1:**
[figure not shown]
Flowchart of TAILOR study. AIH, autoimmune hepatitis; aza, azathioprine; MMF, mycophenolate mofetil; QoL, quality of life; 6-tg, thioguanine; 6-mp, mercaptopurine

## Methods: participants, interventions and outcomes

### Study setting {9}

This multicentre study will be conducted at the gastroenterology and hepatology outpatient clinics of seven academic centres and three large teaching hospitals in the Netherlands. Other Dutch hospitals can recruit patients and refer them to participating hospitals for screening and inclusion. A list of participating centre can be found at ClinicalTrials.gov under NCT05221411.

### Eligibility criteria {10}

#### Inclusion criteria

Patient is older than 18 years old.Probable or definite auto-immune hepatitis according to the original or simplified IAIHG criteria (> 10 points pre-treatment on the original criteria or > 6 points on the simplified criteria) [1, 2].Incomplete responder on at least a half year of first-line treatment, including azathioprine/6-MP/6-TG and prednisolone or budesonide.ALT 1.5–10 × ULN for at least 2 months.Patient is capable of understanding the purpose and risks of the study, has been fully informed and has given written informed consent to participate in the study.

#### Exclusion criteria

Presence of decompensated liver disease, defined as ascites, coagulopathy (INR > 1.5), encephalopathy, variceal bleed, hepato-pulmonal syndrome, hepatorenal syndrome or HCC in the past 6 monthsSigns of other liver diseases as metabolic-dysfunction associated steatotic liver disease (MASLD), Wilson disease, hemochromatosis, alcoholic liver disease or viral hepatitis B/C/DClinical diagnosis of overlap/variant syndrome with PBC or PSCLiver transplantation in the medical history or currently on the waiting list for liver transplantationIncompliance with therapy during the last 12 monthsActive infections during inclusion including latent tuberculosis and HIV co-infectionAllergic or hypersensitive to TAC or MMFAn estimated glomerular filtration rate (eGFR) of < 60 mL/minPregnancy or intention to become pregnant in the next 12 monthsUse of TAC or MMF in the pastMalignancy in the medical history in the past 5 years, or current use of chemotherapy.

### Who will take informed consent? {26a}

Patients are recruited at the outpatient clinics of all participating hospitals as well as in recruiting hospitals. They will be asked to participate by their treating physician. The local principal investigator will explain the study to potential study subjects. Subsequently, patients will receive a patient information form (PIF). After 1 week, patients will be contacted by the central study coordinator, to whom questions can be asked and by whom additional clarification can be given. After having given informed consent, a screening visit (Tx) will be planned.

### Additional consent provisions for collection and use of participant data and biological specimens {26b}

Patients will provide informed consent for the collection of back-up samples of serum and plasma, which will be performed in several centres. These samples will be stored locally and will be used for central end-point analyses. Throughout the study, additional research questions may arise. Ancillary studies can be performed on blood samples.

### Interventions

#### Explanation for the choice of comparators {6b}

Several retrospective studies have reported on the use of TAC as a second-line therapy in autoimmune hepatitis. In several case series, TAC was given to patients unresponsive to prednisone and/or AZA. The first study of TAC in AIH was performed by van Thiel et al [16]. They studied the use of TAC for induction treatment of AIH and found a decrease in ALT in 80% of the patients. In several subsequent (relatively) small case series, TAC was given as second-line therapy for AIH, whereas remission rates differed between 20 and 92% [14, 17–22].

The use of MMF for AIH, both in case of intolerance for first-line treatment and in case of insufficient response, has been published by our group [23]. Retrospective cohort studies indicate that in AIH patients with intolerance or insufficient response on first-line therapy, with MMF complete remission can be induced in 0–22% of patients [23–25]. One study reported a remarkable proportion of 57% remission with MMF [26]. There appeared to be a difference in remission rates between patients started on MMF for intolerance to first-line treatment or for insufficient response to first-line treatment [23–25].

Both TAC and MMF are mentioned as possible second-line therapy in guidelines and literature. In one paper, CR on MMF was reported to be 22% in patients with an incomplete response, which is lower when compared to the CR rate in patients with intolerance to AZA. A cohort of treatment naïve AIH patients has also been treated successfully with MMF [27–29].

Because of a more favourable profile of adverse effects, MMF should possibly be favoured as second-line treatment for AIH, and not TAC, although it might be less effective [30]. TAC could be more effective than MMF as second-line therapy for incomplete response. However, the aforementioned studies are all retrospective cohort studies. No randomised trials for second-line therapies for AIH have been performed.

#### Intervention description {11a}

##### Group one: Prolonged-release tacrolimus (Envarsus®)

For this study, TAC will be used, preferably 0.75 mg, 1 mg and 4 mg tablets of Envarsus® from Chiesi Pharmaceuticals. Envarsus is a once-daily prolonged-release formulation with more stable tacrolimus levels [31, 32]. Patients in this arm will start with oral 0.07 mg/kg/day of meltdose tacrolimus once daily. If Envarsus is unavailable, other forms of TAC (e.g., Advagraf, Adport, Dailiport, Prograft) may be used, with the appropriate dosing scheme, since different forms of TAC have different bioavailability. Tacrolimus has a narrow therapeutic window and highly variable pharmacokinetics. Therapeutic drug monitoring (TDM) will be performed to reach a target AUC of 160 µg h/L (20% interval 128–196) tacrolimus. This is compatible with trough levels of 3.6–7.4 µg/l [33–35]. Tacrolimus can have several adverse effects. Due to a narrow therapeutic window, therapeutic drug monitoring is necessary to prevent underexposure, which can result in reduced effect, and overexposure, which can lead to side effects including hypertension, tremor, headache, renal toxicity and hyperkalaemia. Like with any other immunosuppressive drug, there is an increased risk of infections.

##### Group 2: mycophenolate mofetil (Cellcept®)

For this study, 500 mg tablets of CellCept® from F. Hoffmann-La Roche AG Pharmaceuticals will be used. If not available, generic forms of MMF may be used. Patients in the MMF arm will receive a maximum total dose of 2000 mg daily, split-dose. Patients will commence with a dose of 500 mg twice daily. When tolerated, doses will be titrated to 1000 mg twice daily after week 2. The most common adverse effects are gastrointestinal toxicity, leukopenia, thrombopenia and increased risk of infections.

#### Criteria for discontinuing or modifying allocated interventions {11b}

Subjects can leave the study at any point during the follow-up. Investigators can decide to withdraw a subject from the study when:A flare of AIH (ALT > 10xULN) occursOther urgent medical reasons (e.g. pregnancy (for patients assigned to MMF) or acute (on chronic) liver failure)

In case of severe adverse effects or eGFR <50 ml/min, the dose of study medication will be halved. If severe side effects persist despite halving the dose, study medication will be discontinued. If the eGFR is < 40ml/min, study medication will also be discontinued. In case study medication is discontinued, all follow-up visits and assessments will still be performed with the exception of the therapeutic drug monitoring.

If loss of remission, defined as ALT >1–3× ULN after reaching CR, occurs or when ALT reaches 3×10× ULN during the study, corticosteroid dose will be increased to the dose at screening, while trial participation can be continued as per discretion of the treating physician.

#### Strategies to improve adherence to interventions {11c}

TAC and MMF will be packed and labelled as study medication according to Good Manufacturing Practice (GMP) guidelines by the Department of Pharmacy of the Leiden University Medical Center (LUMC). Local study investigators will perform drug accountability using a drug accountability log. Patients will be asked to take their medication and empty boxes to the close-out visit to control compliance. Additionally, the *Basel Assessment of Adherence to immunosuppressive medIcations Scale* (BAASIS) will be used to check compliance. The questionnaires will be filled out during each clinic visit or will be sent electronically by e-mail. Reminders will be sent after 14 days.

#### Relevant concomitant care permitted or prohibited during the trial {11d}

New medication may be prescribed at the discretion of the treating physician. No new immunosuppressants may be used, besides the corticosteroids already in use at screening. If a flare of AIH (ALT > 10 × ULN) occurs during the study period, patients will receive the standard of care from the treating physician and trial participation will end. Study subjects are not allowed to participate in other trials investigating pharmaceutical agents for AIH.

#### Provisions for post-trial care {30}

Participants who suffer harm from participating in the study are covered by the liability insurance of the LUMC with a maximum of €650,000 per subject, €5,000,000 per study and €7,500,000 per year. The insurance applies to the damage that becomes apparent during the study or within 4 years after the end of the study.

#### Secondary outcomes

The secondary objectives are:Safety and tolerability—number and severity of side effects; rate of stopping treatment due to side effects; serum creatinine and potassium; blood pressure; blood glucose levels and incidence of new-onset diabetes; number of (opportunistic) infections; tremor; diarrhoeaProportion of patients with CR after 6 monthsCumulative corticosteroid doseChange of AST, ALT and IgG at 6 and 12 months versus baseline and between groups at the same time pointsLiver function: total bilirubin, albumin, INR and MELD-score after 6 and 12 months between groupsFibrosis: liver stiffness as measured by elastography and blood fibrosis markers (Enhanced Liver Fibrosis test)Quality of life (questionnaires) using the validated liver disease symptom index (LDSI), short-form 36 (SF-36) and EQ5DCost-effectiveness: using modified Productivity Cost Questionnaire (iPCQ) and Medical Consumption Questionnaire (iMCQ) questionnaires

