### Data collection and management

#### Plans for assessment and collection of outcomes {18a}

At the screening visit, data on demographics, medical history and medication use is collected after obtaining informed consent. Simultaneously laboratory assessments are done, including screening for systemic infections and pharmacogenetics, and VCTE is performed. After inclusion, participants visit the outpatient at different timepoints (Table 1). During these visits, laboratory tests are done, TDM is done using the area under the curve measurements (visits T_2_ and T_12_) or trough levels (only for TAC on visits T_24_, T_36_, T_52_), and (serious) adverse events ((S)AEs) are reviewed. During specified study visits, health-related quality of life (HRQoL) questionnaires are administered and VCTE is done.

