#### Adverse event reporting and harms {22}

AEs are defined as any undesirable experience occurring to a subject during the study, whether or not considered related to the investigational product. All adverse events reported spontaneously by the subject or observed by the investigator or his staff will be recorded. A SAE is any untoward medical occurrence or effect that (a) results in death; (b) is life-threatening (at the time of the event); (c) requires hospitalisation or prolongation of existing inpatients’ hospitalisation; (d) results in persistent or significant disability or incapacity; (e) is a congenital anomaly or birth defect; and (f) requires medical or surgical intervention to preclude of any other important medical event that did not result in any of the outcomes listed above due to medical or surgical intervention but could have based upon appropriate medical judgement. Elective hospital admissions are not considered SAEs. The principal investigator of the participating site will report the SAE to the coordinating investigator within 24 h. The latter will report the medical ethical committee via Toetsingonline.nl within 7 (death) or 15 (life threatening event) days.

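### Leukopenia and thrombopenia, named among the commonest MMF effects, have no safety outcome of their own, whereas the named laboratory effects of tacrolimus do

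*Protocol article*

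**What the plan says.** All references are to the protocol article.

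- **Intervention description, tacrolimus group:** overexposure can cause "side effects including hypertension, tremor, headache, renal toxicity and hyperkalaemia". Infection is added as a class effect: "Like with any other immunosuppressive drug, there is an increased risk of infections".
- **Intervention description, MMF group:** "The most common adverse effects are gastrointestinal toxicity, leukopenia, thrombopenia and increased risk of infections".
- **Secondary outcomes, safety and tolerability:** the list opens with two generic items for both arms, "number and severity of side effects; rate of stopping treatment due to side effects". Specific items follow: "serum creatinine and potassium; blood pressure; blood glucose levels and incidence of new-onset diabetes; number of (opportunistic) infections; tremor", and lastly diarrhoea. There is no leukocyte, platelet or cytopenia item.
- **Adverse event reporting and harms {22}:** "All adverse events reported spontaneously by the subject or observed by the investigator or his staff will be recorded". No laboratory threshold for calling an abnormal value an adverse event is given there.
- **Who will be blinded {17a}:** patients and all research staff know the assigned arm. Only the outcome assessors are blinded, at the analysis stage.
- **Plans for assessment and collection of outcomes {18a}:** "During these visits, laboratory tests are done", and adverse events are reviewed at the same visits. The text does not list the laboratory panel, and Table 1 is not reproduced.
- **Explanation for the choice of comparators {6b}:** "Because of a more favourable profile of adverse effects, MMF should possibly be favoured as second-line treatment for AIH". The article adds that MMF may be the less effective drug.

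**The concern.** Safety is part of the stated aim, and the article frames the choice between the drugs as possible extra efficacy of tacrolimus against possibly better tolerability of MMF. The tolerability premise is therefore itself under test, and the Discussion expects the answer to inform guidelines.

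For that comparison, each drug's known toxicities should be ascertained in the same way. A rise in creatinine or potassium will appear in the results because the value itself is an outcome. A fall in leukocytes or platelets without symptoms will appear only if someone at the site, knowing the treatment, decides to record it as an adverse event. Blinding the assessors at the analysis stage cannot restore an event that was never recorded. If such falls are recorded patchily, the safety tables will describe one drug's silent laboratory effects more completely than the other's.

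**Working it through.** The plan gives no figure on this point, such as an expected cytopenia rate. The sample size of 86 rests on response proportions only and is not affected. The check is a mapping of each named toxicity to the list of safety outcomes.

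| Drug | Named effect | Dedicated safety item |
|---|---|---|
| Tacrolimus | hypertension | blood pressure |
| Tacrolimus | tremor | tremor |
| Tacrolimus | headache | none |
| Tacrolimus | renal toxicity | serum creatinine |
| Tacrolimus | hyperkalaemia | potassium |
| Tacrolimus | infections | infections |
| MMF | gastrointestinal toxicity | diarrhoea |
| MMF | leukopenia | none |
| MMF | thrombopenia | none |
| MMF | infections | infections |

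**Counts**

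- All named effects: tacrolimus 5 of 6, MMF 2 of 4.
- Without infections, which both drugs share: tacrolimus 5 − 1 = 4 of 6 − 1 = 5; MMF 2 − 1 = 1 of 4 − 1 = 3.
- Named laboratory effects only: tacrolimus 2 of 2 (renal toxicity, hyperkalaemia); MMF 0 of 2 (leukopenia, thrombopenia).

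Glucose and new-onset diabetes are safety outcomes, but the tacrolimus section does not name them as effects of that drug. They are left out of both counts.

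**How a silent cytopenia reaches the results.** There are two routes: the count of side effects, if it is recorded as an adverse event, and the rate of stopping, if it leads to stopping. Both need a person to notice and classify it. A creatinine or potassium value needs no such step.

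**Direction.** Let p be the true proportion of patients with a low count in an arm, and r the fraction of these recorded as adverse events. The recorded difference is r(MMF) × p(MMF) − r(TAC) × p(TAC).

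- If r is the same in both arms and below 1, the recorded difference is r times the true one. A true excess on MMF would be understated.
- If staff who expect cytopenia on MMF look harder for it there, r(MMF) exceeds r(TAC) and the error can go the other way.

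The documents give neither p nor r, so no size can be computed.

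**The case against.** The strongest reply is that cytopenias are already inside the safety comparison. The two generic items apply to both arms, and the article itself calls leukopenia and thrombopenia adverse effects, so they fall under those items. The adverse event definition is broad and includes what staff observe. Laboratory tests and adverse event review happen at the same visits, so a low count on a report can be seen and recorded. The statistical methods section also says that all parameters will be summarised by group; if blood counts are in Table 1, a between-arm summary may already be intended. Finally, a journal article leaves laboratory panels, thresholds and safety tables to the full protocol or the analysis plan.

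Most of this stands, and it limits the point. It rules out saying that cytopenias are left out of the safety comparison or that blood counts are not measured. What can be said is that 0 of 2 are named as outcomes.

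It does not remove the mismatch. The published outcome list is detailed down to potassium and tremor, so the selection of named items is a choice made in this document. If generic capture were enough for laboratory effects, creatinine and potassium would not have needed their own items either. Drawing a test at a visit also does not make it a prespecified between-arm comparison.

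**Conclusion.** The dedicated safety outcomes are asymmetric. Both named laboratory toxicities of tacrolimus have a measured item; neither of the two named for MMF has one. Across all named effects the coverage is 5 of 6 against 2 of 4. Leukopenia and thrombopenia depend on generic items fed by open-label adverse event recording, so silent falls in counts may be ascertained less systematically.

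A reader might infer that the safety comparison is tilted toward MMF. The documents do not support that. Under-recording would plausibly flatter MMF, but arm-dependent vigilance could work in the opposite direction, and there is no rate from which to calculate either. Nor does the comparators section fix MMF as the safer drug: its wording is hedged, and it notes that the evidence is retrospective.

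The conclusion assumes that the outcome list in the article is the operative one and that adverse events are recorded as the harms section describes. If the full protocol or analysis plan already names blood counts as safety outcomes, only the published list needs correcting. The primary endpoint is not affected. This is a worthwhile and cheap improvement to a secondary comparison, not a threat to the trial.

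**What to change.** Add leukocyte and platelet counts to the safety outcomes, in both arms and at the same visits as creatinine and potassium. For each parameter, compare the measured values and the proportion of patients below one common laboratory threshold, whether or not the site recorded an adverse event. The threshold serves reporting only and implies no change to treatment rules.

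The cost is a few eCRF fields and one more safety table. If counts are not already in the visit panel, it also means a routine add-on test to blood drawn at those visits. The article reports 5 of 86 patients randomised when it was written, so on that status nearly all patients could be covered prospectively. For those already enrolled, counts could be entered where they were measured.
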